### Secondary endpoints

2.8

Nine secondary endpoints will be evaluated. Specifically:
1.Acute procedural success of AF ablation. The acute success of the AF ablation is verified by the completion of the necessary ablation application(s), the validation of ablation through appropriate technique(s), and, when applicable, the termination of the primary arrhythmia.2.Recurrence of AF‐only arrhythmia after 12 months from the procedure.3.Occurrence of all kinds of atrial arrhythmias. A sustained atrial flutter/atrial tachycardia is defined as >30 seconds arrhythmia occurrence as recorded on a monitoring device.4.Percentage of patients free from any clinical atrial arrhythmias according to procedure type (de novo vs. redo ablation).5.Association between baseline patient's characteristics and electroanatomical variables derived from the evaluation of voltage and activation maps and arrhythmias' occurrence at 12 months.6.Repeated ablation procedures (after the index procedure). The number of ablation procedures for the treatment of the primary arrhythmia after the index procedure.7.Procedure‐related adverse events: number, type, and rate of the adverse events that occur during the procedure and during 12 months follow‐up.8.Patient‐reported outcomes: EQ‐5D‐5L, Specific Symptom Scale Score, and EHRA Score of AF‐related Symptoms.9.Health Economic units: resource consumption and the associated costs in terms of ablation procedures, follow‐up, management of complications, and health care resources utilization.

### Additional analyses

2.9

Additional evaluations will be performed. Specifically, the incidence and location of antral low‐voltage activation targets and the rate and location of any PV reconnection after first pass ablation will be evaluated.

### Statistical methods and data analysis

2.10

Continuous data are expressed as mean ± standard deviation or median values with interquartile range for all the variables collected on the entire population or specific subgroups. Continuous variables will be compared by means of Student *t* test, analysis of variance, or nonparametric test (median test or Mann–Whitney *U* test). Categorical data will be compared by means of the *χ*
^2^ test (Pearson, Yates, or Fisher exact test, as appropriate). Baseline clinical variables, peculiar parameters of the ablation/mapping system, procedural, and postprocedural variables will be tested by regression analysis to evaluate their association with the primary and secondary endpoints. Therefore, independent predictors will be identified by multivariate regression.

Risk estimations (“hazard ratio” 95% confidence interval) will be presented together with the cumulative survival curves (Kaplan–Meier) and the frequency of events (per 100 person‐years) in each group. A specific univariate and multivariate analysis will be carried out to identify the most predictive factors of outcome in a short‐ and long‐term period. A *p* value of 0.05 will be considered statistically significant.

### Sample size justification

2.11

The DELETE AF study is designed to be observational and comparisons to published data will be done in a post hoc fashion. The sample size requirements for this study are intended to provide adequate power for the analysis of the primary objective.

Assumptions and their rationale:
75% Atrial arrhythmias recurrence‐free rate (performance goal set according to published data).^15^, ^16^, ^17^, ^18^
Both large, multicenter randomized clinical trials^16^, ^17^ and pooled results^15^ that compared the two most common ablation approaches (RF ablation and cryoablation) demonstrated that the efficacy of cryoablation was noninferior to RF ablation at 12 months. In a very recent metanalysis,^18^ the most advanced RF ablation technology was associated with higher freedom from AF/atrial tachycardia at 12 months, compared with conventional ablation catheters in paroxysmal AF patients (75.6% vs. 64.7%; *p* = .015).85% Expected performance in the study groupIn a single‐centre study, Segerson et al.^8^ demonstrated a 90.7% recurrence‐free rate in patients who underwent high‐density mapping (HDM)‐guided PVI and subsequent mapping and ablation of concealed low‐voltage signals through a structured workflow vs. a 73.9% recurrence‐free rate in the group of historical controls who underwent traditional PVI alone. Considering the multicenter setting of the present study, the variable number, and the experience of the operators performing ablation procedures, we set this cutoff to 85%.Actual power 90% (*β* level set at 0.1)The proportion of patients free from any clinical atrial arrhythmias (primary objective) will be measured in the subgroup of “Treatment” subjects. The number of “Attempt” patients (subjects the procedure is not performed according to the prespecified workflow) is not known. Therefore, the enrollment phase will continue until 200 patients are included in the “Treatment” group (190 patients + 5%, i.e., maximum expected attrition rate during follow‐up), up to a maximum of 300 subjects.

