### Study hypotheses

2.6

This prospective cohort study has been specifically designed to demonstrate a low rate of clinical atrial arrhythmia recurrence with an improved procedural PVI workflow^8^ for catheter ablation of PAF in a multicenter setting, using the most advanced point‐by‐point technology versus recent literature reference on ablation of PAF.^15^, ^16^, ^17^, ^18^

Apart from its primary purpose, the study will evaluate the association between the occurrence of atrial arrhythmias and baseline patient's characteristics (clinical history and drug therapy) or procedural data (post hoc voltage and activation maps analysis), will estimate costs associated with the use of health care resources, rate of the adverse events associated with the primary ablation procedure, and overall procedure time. Moreover, periprocedural factors (e.g., periprocedural anticoagulation management or total fluoroscopy time and contrast medium utilization) associated with the 12‐month outcome and the acute procedural success will be investigated.

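### The 90% power is claimed for a comparison with a 75% goal taken from the literature, but the same section declares comparisons with published data post hoc

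*Protocol article*

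**What the plan says.** - **Protocol article, 2.6 Study hypotheses.** The study "has been specifically designed to demonstrate a low rate of clinical atrial arrhythmia recurrence", and the sentence goes on to set this against recent literature on ablation of paroxysmal AF.
- **2.11 Sample size justification, opening.** The study is called observational and "comparisons to published data will be done in a post hoc fashion". The next sentence says that the sample size is meant to give adequate power for the primary objective.
- **2.11, assumptions.** The 75% recurrence-free rate is a "performance goal set according to published data". The expected rate is 85%, lowered from a single-centre 90.7%, with the words "we set this cutoff to 85"%. Power is given as "Actual power 90"%.
- **2.11, size.** The primary proportion "will be measured in the subgroup of" Treatment subjects. Enrolment runs to 200 such patients ("190 patients + 5"% for attrition), with a ceiling of 300 subjects overall.
- **2.10 Statistical methods and data analysis.** It lists t test, analysis of variance, nonparametric tests, the chi-square family, regression, Kaplan–Meier curves and hazard ratios. A p "value of 0.05 will be considered statistically significant". No sidedness is given, and no test or interval is linked to the 75% goal.

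**The concern.** The 75% goal is itself a figure from published data. Comparing the observed rate with it cannot be both the analysis that the study is powered for and a post hoc comparison. If the post hoc sentence is followed, the trial yields an observed percentage and a later comparison with some literature figure. Power and type I error are properties of a rule fixed in advance, so neither would then be defined for the main claim.

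The article gives several figures that could serve as reference: 64.7% (conventional catheters) and 75.6% (advanced RF technology) from the cited meta-analysis, 73.9% (historical controls in the single-centre study), and the 75% goal. In a single-arm study, the reference value is the whole control condition, so leaving it open matters more than it would in a randomised trial.

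**Working it through.** **Inputs.** Goal p0 = 0.75, expected rate p1 = 0.85, power 90% and n = 190 evaluable come from 2.11. The 0.05 level comes from 2.10. Sidedness is not stated, so two-sided 0.05 (upper tail 0.025) is assumed, and one-sided 0.05 is shown as the alternative.

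**Step 1: which comparison does the stated size fit?**

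One-sample normal approximation: n = [(z_α·√(p0(1−p0)) + z_β·√(p1(1−p1))) / (p1−p0)]²

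- Two-sided 0.05: [(1.960·√0.1875 + 1.2816·√0.1275)/0.10]² = [(0.8487 + 0.4576)/0.10]² = 170.6, so 171.
- One-sided 0.05: the same with 1.645 gives 136.9, so 137.
- Exact binomial: power is at least 90% for every n from 183 (upper tail 0.025) or from 153 (upper tail 0.05).
- A two-group comparison of 75% with 85% would need 335 per group.

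So 190 is of the order of a one-sample comparison with a fixed 75% and far from a two-group design. It is somewhat above the minimum, which is conservative. Attrition: 190/0.95 = 200, as stated.

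**Step 2: what would 190 deliver if the comparison were prespecified?** With X ~ Binomial(190, p), take the smallest r with P(X ≥ r | 0.75) ≤ α.

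| Level | Success if | True α | Power at 85% |
|---|---|---|---|
| Two-sided 0.05 (upper tail 0.025) | X ≥ 155 (81.6%) | 0.0197 | 91.9% |
| One-sided 0.05 | X ≥ 153 (80.5%) | 0.0442 | 96.3% |

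The exact two-sided 95% confidence interval gives the same rule as the first row: its lower limit is 75.3% at 155/190 and 74.7% at 154/190. The claimed 90% is met under either choice.

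**Step 3: what does an open reference do?** Same exact rule (upper tail 0.025, n = 190), with each rate quoted in 2.11 as reference. The last column is the chance of a significant result when true freedom from recurrence is 75%, that is, no better than the study's own goal.

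| Reference | Minimum successes | P(significant, true rate 75%) |
|---|---|---|
| 64.7% | 137 (72.1%) | 84% |
| 73.9% | 153 (80.5%) | 4.4% |
| 75% | 155 (81.6%) | 2.0% |
| 75.6% | 156 (82.1%) | 1.3% |

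The reference therefore affects the conclusion when the observed rate lies between about 72% and 82%. If the study observes what it expects (162/190 = 85.3%), the exact 95% interval is 79.4% to 90.0% and clears all four.

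**The case against.** The strongest reply is that the benchmark is already public. The 75% is named in the article as the performance goal, with sources and a rationale, and 2.6 makes the comparison with the literature part of the hypothesis. On this view, post hoc only means that a study without a concurrent control is set beside external data once its own data are in. The 64.7% figure is also an unlikely choice, because it describes conventional catheters and the goal was set close to the advanced-technology rate. These points stand in part. They make a late switch of reference less likely, but the words still exempt the powered comparison from prespecification.

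Four stronger readings might tempt a reader, and the document does not support them.

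- *No listed method could test one arm against 75%.* The Pearson chi-square in 2.10 can be used with one sample. At n = 190 the expected count is 142.5, so 155 successes give (155 − 142.5)²/(190·0.75·0.25) = 4.39 and 154 give 3.71, against a critical value of 3.84. That is the same threshold as the exact test. What is missing is the link between test and goal. A condensed article may leave that link to the full protocol or analysis plan, so its absence alone would not be a finding.
- *No alpha is given.* Section 2.10 gives 0.05. Only the sidedness is open.
- *190 is wrong because it is not the exact output of a standard formula.* It exceeds the minimum and delivers the stated power.
- *85% is the success threshold, so power is only about one half.* The word cutoff is loose, but it stands under the heading of expected performance and explains why 90.7% was lowered. The goal is separately named as 75%.

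**Conclusion.** The contradiction holds and lies within section 2.11 itself, reinforced by 2.6. The 90% power is claimed for a comparison that the text declares post hoc. Naming a test in a document not shown here would not by itself reconcile the two statements.

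The defect concerns the status of the primary comparison and leaves the number of patients unaffected. With 190 evaluable patients and an exact test at two-sided 0.05 against 75%, power at a true 85% is about 92%. With the reference left open, the chance of a significant result at a true rate of 75% runs from 1.3% to 84% across the rates that the article quotes. The 84% is the extreme case and assumes that 64.7% is chosen after the data are seen. Nothing in the article suggests that this is intended.

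These figures assume 190 evaluable patients, a binary 12-month outcome known for each, and a two-sided 0.05 level. Since the point bears on the primary claim and is easily corrected, it should be settled before outcomes are known.

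**What to change.** 1. In 2.10 and 2.11, make the comparison with 75% the prespecified primary analysis: H0 p ≤ 0.75 against H1 p > 0.75, where p is 12-month freedom from atrial arrhythmia in the Treatment group. Declare success if the lower limit of the exact two-sided 95% confidence interval exceeds 75%.
2. State the criterion through the confidence limit and not as a fixed count, since the evaluable number will vary. The count can be given as an example: at least 155 if 190 are evaluable.
3. State that the 0.05 level is two-sided for this test and that power is about 92% at 85% with 190 evaluable patients.
4. Confine post hoc to other comparisons with the literature, and label those descriptive.
5. Call 85% the expected rate and drop the word cutoff.

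If the sponsor does intend every literature comparison to be post hoc, the consistent alternative is to remove the power claim and justify the size by precision: 1.96·√(0.85·0.15/190) = 0.051, about ±5.1 percentage points at 85%.

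Either route costs a few sentences in the protocol and analysis plan, with no added patients or data.

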### Ablation treatment

2.4

All procedures will be performed under conscious sedation or general anesthesia according to centers' preference. All patients will be treated according to a prespecified structured workflow followed by each center. After single or double transseptal punctures under fluoroscopic guidance, intravenous unfractionated heparin boluses will be administered, to maintain an activated clotting time of >300 seconds. The basket mapping catheter (Orion^TM^; Boston Scientific) and the ablation catheter (IntellaNav MiFi OI^TM^ or IntellaNav StablePoint OI^TM^; Boston Scientific) will be then inserted through steerable sheaths. The Orion^TM^ catheter will be used in combination with the Rhythmia^TM^ HDx mapping system to create a three‐dimensional electroanatomical voltage and activation map of the left atrium. The ablation target in all patients will be PVI and the achievement of complete electrical quiescence within the antral region. PVI will be performed by means of RF energy in a point‐by‐point ablation pattern by the open‐irrigated ablation catheter. Point‐by‐point RF delivery will be performed in such a way as to create contiguous ablation spots encircling the PVs. The maximal interlesion distance between two neighboring lesions will be set ≤6 mm. Ablation will be guided by the magnitude and time course of the impedance drop during RF delivery.^9^, ^10^, ^11^ Power settings will be set at the individual operator's discretion, within the range of 30–50 W, depending on the left atrial segment considered.

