The endpoint of ablation is PVI, as assessed on the basis of entry and exit block by means of the 64‐pole Orion^TM^ catheter placed sequentially in each of the PVs, and the achievement of complete electrical quiescence within the antral region. The Lumipoint^TM^ map analysis tool, which automatically identifies fragmented potentials and continuous activation, will be used sequentially on each PV component, to assess the presence of PV gaps (PVGs) and RAPs and to characterize electrical propagation. After identification of an atrial site with PVG or RAP by means of the Lumipoint^TM^ software, both the voltage map and the standard activation/propagation map will be investigated to check for agreement. Regarding the ablation strategy, each residual PVG will be first targeted to guarantee contiguity in the lesion set. Second, after confirmation of bidirectional isolation, when any low‐voltage propagation is suspected within the region of previous antral ablation and are confirmed by information from the Lumipoint^TM^ tool and by consistency with regional activation timing,^8^ additional focal ablations will be performed. These ablations will be then reassessed by means of repeat Lumipoint^TM^ and voltage and propagation mapping until electrical quiescence will be achieved. A detailed description of the procedural workflow is depicted in Figure 2. Example of the ablation workflow, identification of PVGs and residual RAPs detected through Lumipoint^TM^ according to the procedural workflow and demonstration of PVI, and complete electrical quiescence at the end of the ablation are reported in Figure 3A–C.

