### Primary endpoint

2.7

The primary endpoint of the study is the rate of success at the medium‐term follow‐up after PVI in consecutive patients undergoing AF ablation. Specifically, the primary outcome measure of this study is the percentage of patients with documented arrhythmias after 12 months from the procedure. Arrhythmias are defined as any AF, atrial flutter, or atrial tachycardia episode, continuously for >30 seconds, as recorded by any postablation ECG modality. Arrhythmia recurrences within the first 3 months (blanking period) are classified as early recurrences and will not be considered a procedural failure.

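### The primary success rate is restricted to patients whose procedure followed the workflow, while the endpoint is defined in consecutive ablation patients; this may bias the comparison with the 75% goal upward, by an unknown amount

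*Protocol article*

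**What the plan says.** Section 2.7 (Primary endpoint) sets the endpoint as the success rate "after PVI in consecutive patients undergoing AF ablation". Section 2.2 shows that these consecutive patients are the ones enrolled after consent. Section 2.4 (Ablation treatment) adds: "All patients will be treated according to a prespecified structured workflow followed by each center".

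Section 2.11 (Sample size justification) names a narrower group: "The proportion of patients free from any clinical atrial arrhythmias (primary objective) will be measured in the subgroup of" Treatment subjects. The others are Attempt patients, described as "subjects the procedure is not performed according to the prespecified workflow", and their number is said to be unknown. Enrolment runs until there are 200 Treatment patients (190 plus 5% attrition), with a maximum of 300 subjects. The performance goal is 75% free of recurrence, the expected rate is 85% and the power is 90%.

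In Section 2.4 the workflow ends with repeat mapping and focal ablation "until electrical quiescence will be achieved".

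**The concern.** The two sections give different denominators for the same primary result. The one in Section 2.11 is formed after treatment has begun, because nobody can know beforehand whether a procedure will follow the workflow. The final step of that workflow is itself an acute result. A patient in whom quiescence is not reached, or whose procedure is cut short, may therefore be classed as Attempt and leave the analysis. The Introduction's premise is that residual antral potentials are weak points whose ablation improves freedom from AF. On that premise, such patients would be expected to do worse, and leaving them out would raise the observed rate.

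The aim is also at stake. The Discussion says that the single-centre result has not been shown across centres and depends on operators' interpretation and skill. Section 2.11 lowers the expected rate from 90.7% to 85% partly because operators' experience varies. Whether operators elsewhere can deliver the workflow is thus part of the question, yet the analysis set removes the cases where they did not.

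This is not a detail left to an analysis plan. The article itself states the primary set, and it describes no test of the 75% goal in all treated patients.

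**Working it through.** **Inputs from Section 2.11.** Goal 75%; expected rate 85%; power 90%; 190 evaluable; 200 Treatment patients; cap 300. Two recurrence-free rates there serve as reference values for Attempt patients: 73.9% (historical controls with traditional PVI alone) and 64.7% (conventional catheters in the cited meta-analysis).

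**Assumptions.** Section 2.10 says only that a *p* "value of 0.05 will be considered statistically significant", without sidedness. I take 0.025 in the upper tail of an exact binomial test. The number of Attempt patients and their success rate q are not given, so both are varied.

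**Step 1. The plan's own figure.** With n = 190 and p0 = 0.75, the smallest count with upper-tail probability at or below 0.025 is 155 (81.6%).
- P(X ≥ 155 | 0.75) = 0.0197.
- P(X ≥ 155 | 0.85) = 0.919.
- 190 / (1 − 0.05) = 200.

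The stated size is adequate for the Treatment set. The question is the analysis set, not this arithmetic.

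**Step 2. How many can be left out.** If the target of 200 is met at the cap, 300 − 200 = 100 patients, or 33% of enrolment. Two milder cases are 22 of 222 (10%) and 50 of 250 (20%).

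**Step 3. Chance of beating 75% when the all-attempted rate is exactly 75%.** With N enrolled and A = N − 200 Attempt patients, the implied Treatment rate is

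p_T = (0.75 × N − q × A) / 200.

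Example: N = 300, q = 0.647 gives (225 − 64.7) / 200 = 0.8015. The false-success chance is P(X ≥ 155 | n = 190, p_T).

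| Attempt / enrolled | p_T, q = 73.9% | Chance | p_T, q = 64.7% | Chance |
|---|---|---|---|---|
| 22 / 222 | 75.1% | 2.2% | 76.1% | 4.4% |
| 50 / 250 | 75.3% | 2.4% | 77.6% | 10.6% |
| 100 / 300 | 75.6% | 2.9% | 80.2% | 34.9% |

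If Attempt patients also succeed in 75%, the chance is 2.0% in every row, which is the size of the test itself.

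**Step 4. Power if all attempted patients are analysed.** With Treatment at 85% and Attempt at 73.9%, the overall rate is (200 × 0.85 + A × 0.739) / N. It is treated as a single binomial proportion, before attrition.

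| Enrolled | Overall rate | Successes needed | Power |
|---|---|---|---|
| 222 | 83.9% | 180 | 89% |
| 250 | 82.8% | 202 | 82% |
| 300 | 81.3% | 240 | 75% |

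**The case against.** A reader might infer that the restriction certainly inflates the result, and by a lot. If Attempt patients succeeded in only 60%, the chances in Step 3 would be 6%, 19% and 67%. The documents do not support that reading. A rate of 60% lies below every recurrence-free rate they give (64.7%, 73.9%, 75.6%, 90.7%), and 67% also needs the maximum number of exclusions. The closest stand-in for a patient who receives PVI without the antral step is arguably 73.9%, where the effect is negligible. The Attempt definition is also broader than an uncompleted workflow. It would cover a skipped mapping step or a deviation unrelated to prognosis, and nothing says that failing to reach quiescence alone makes a patient Attempt. This part of the objection stands: the direction is plausible but not proven, and the size is unknown.

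Four further points can be made for the plan.
- The set is declared in advance, and Section 2.7 could be using the word consecutive for enrolment only. Even so, Section 2.7 does not mention the restriction, and the two sections need reconciling.
- The study is called observational, with post hoc comparisons to published data, and the 155-of-190 rule is my assumption. That is fair, but Section 2.11 also sets a performance goal and 90% power for the primary objective, so the denominator matters.
- The 85% expectation comes from patients who underwent the full workflow, so a Treatment set matches that assumption. Whether the studies behind the 75% goal made similar exclusions cannot be judged from this article.
- Section 2.5 follows all patients, and several secondary endpoints carry no Treatment-only restriction. That makes the remedy easy, but none of them is said to test 75% in all treated patients.

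**Conclusion.** The concern holds as a possible upward bias and a conflict over the primary population. Section 2.11 measures the primary proportion in a group formed by how the procedure went, Section 2.7 defines it in consecutive patients, and up to 100 of 300 enrolled can drop out of the result. With the all-attempted rate at exactly 75%, the chance that the Treatment-only test beats the goal stays at 2-3% if Attempt patients do about as well as traditional PVI (73.9%). It rises to 4%, 11% or 35% at 64.7%, for Attempt shares of 10%, 20% or 33%. These figures rest on an assumed one-sided 0.025 exact test and on assumed Attempt numbers and success rates. Apart from any bias, a Treatment-only result cannot show how the workflow performs as attempted across centres, which is what a multicentre validation should answer.

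**What to change.** Reconcile Sections 2.7 and 2.11 by making every enrolled patient in whom the index ablation was started (Treatment plus Attempt) the primary set tested against 75%. Keep Treatment-only as a supportive analysis, and restate power for the new set using Step 4 or the sponsor's own assumptions. If the sponsor keeps Treatment-only as primary, the minimum is to report the all-attempted proportion and its test against 75% with equal prominence.

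In either case, lock each patient's Treatment or Attempt label at the end of the procedure, before any follow-up rhythm data are seen.

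The cost is mainly wording in the two sections and the analysis plan, since follow-up of all patients is already planned. The downside is a somewhat lower headline rate if Attempt patients do worse, and a less favourable stated power: the enrolment rule can stay, but at 73.9% among Attempt patients the power falls below the stated 90%, slightly at 22 of 222 and clearly at 50 of 250 or 100 of 300.
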